# Study protocol: an early intervention program to improve motor outcome in preterm infants: a randomized controlled trial and a qualitative study of physiotherapy performance and parental experiences

**DOI:** 10.1186/1471-2431-12-15

**Published:** 2012-02-15

**Keywords:** Preterm infants, early intervention, Physiotherapy, Motor development, Parental experience

## Abstract

**Abstract:**

**Trial registration:**

ClinicalTrials.gov NCT01089296

## Background

Preterm children are at increased risk of motor impairments and these impairments often persist into adolescence [1]. Evidence regarding the effect of physiotherapy to improve motor development in preterm infants is limited [2]. Interventions designed for promoting development in these infants have been heterogeneous and studies reporting a significant impact of early intervention on motor development are sparse [2,3]. Examining an approach in which the therapy is adapted to the individual premature infant's needs may contribute to knowledge about how to enhance motor development in these infants. To that end we designed a study on the effects of physiotherapy in infants born prematurely as well as on professional performance and parents experiences. The intervention is performed before the infant's reach term age.

The study, named "The Norwegian Physiotherapy Study in Preterm Infants" (NOPPI), consists of a pragmatic randomized controlled trial and a qualitative observational and interview study. The project provides a new approach to intensive physiotherapy consisting of several more elements than today's traditional approach. The intervention integrates key elements from the modified version of the Mother-Infant Transaction Program performed in a study by Kaaresen and colleagues [4,5], as well as elements from interventions in other studies which have shown a positive effect on premature children's motor development [2,3,6-9]. NOPPI explores the effects of individually customized physiotherapy on preterm infants before they reach term age as well as assess the physiotherapy performance and parental experiences of participating in carrying out the intervention in the neonatal intensive care unit (NICU). Outcomes are measured up to two years of age.

The theoretical framework related to the physiotherapy intervention in this study is knowledge of newborn behaviors [10,11], the importance of parental competency [5,12] and theories of motor development, including neuroscience and phenomenology of the body [13-15]. A brief presentation of the framework follows.

### Newborn behaviour and parental competency

Competency in behavioral organization makes active social participation possible for infants [10,11]. As a group, however, prematurely born infants with very low birth weight, and particularly those with serious complications, are reported to have more difficulties in behavioral regulation than infants born at term [16,17]. This may be expressed by the infant as irritability, requiring a long time to settle into a routine and fluctuating attention. Infants' neurobehavioral functioning unfolds through maturation and experience, and the individual can be helped to self-regulate by the caregiver and environmental adaptations. Parental competency to read and understand the individuality and needs of their infant is significant in decreasing parental stress [5] and enhances cognitive outcome and social functioning in the infants [18].

### Phenomenology of the body

The body forms the base from which both the infant as a person and the world are constituted. A newborn's body is a tactile-kinesthetic body. Through moving, infants learn and experience movements by which kinesthetic competency develops [19,20]. On the basis of innate spontaneous movements, the infant learns to know their own body as well as gaining knowledge and realization of the surroundings. Their bodies are both expressive and experienced at the same time. Thus, child development can be understood as a result of interaction among the system consisting of perception, sensation and movement.

### Theory of motor development

The motor development of a child is non-linear [21,22] and regarded as a product of both genetic processes and experiences [23,24]. In dynamic systems theory [25], motor development is believed to be a feedback process based on interaction among different subsystems in the child, the environment and the task. There is a shift from trial and error phases of instability to stable movement in which the synergy of appropriate movements is used to perform a functional task [23]. The motor patterns of healthy children appear flexible, adaptable and dynamic [23].

The motor patterns of preterm infants are dominated by extension and to a lesser degree flexion when compared to infants born at term [26]. This fact, in addition to possible brain damage, may influence the children's spontaneous motor experiences and the process of developing stable motor strategies as they grow. Motor function is related to the development of postural control which is necessary to transfer and modify body weight distribution for appropriate functional movement, communication and social interaction [27,28]. To have postural control is then about maintaining a bodily position over time, regaining postural stability after perturbations, managing changes between different postures, and integration of postures into locomotion and exploration [27]. Interventions that optimize postural control and selective movement in preterm infants may therefore be important in reducing the degree of delayed motor development or the severity of cerebral palsy (CP).

The human brain in infancy is highly plastic and there is an active growth of dendrites and formation of synapses. Experience influences and models the brain and leads to structural changes [24,29] in, e.g., the number of synapses that are developed, the synapses' position and functioning, as well as elimination of synapses that are not needed. Motor skills may be highly influenced by early intervention because the motor pathways forming the corticospinal tracts already show mature myelin at term age [30] and myelination may be activity-dependent [31].

There is some evidence that recovery from central nervous system injury in infants can be understood both by new growth of motor neurons and creation of new synapses. Moreover that part of the brain is not yet developed for specific tasks and may be developed for other uses than were originally intended [24]. Of these insights about brain plasticity it is suggested that early-targeted customized individual intervention could be of great importance to the development of movement quality and function of preterm children.

## Methods/Design

NOPPI consists of two related parts. The aim of the first part, the pragmatic randomized controlled trial, is to evaluate the effect of customized physiotherapy on preterm infants' motor development when the intervention is performed by the parents during a period of three weeks while the infant resides in the NICU. The endpoint is motor development at 24 months of corrected age (CA).

The aim of the second part, the qualitative observation and interview study, is one: to analyze and identify aspects of physiotherapy performance important for teaching parents practical knowledge, and two: to increase our knowledge about parents' experiences of active involvement in implementation of the intervention designed to promote their child's motor development, as well as the short and long term effects on the parent-child relationship. The endpoint is 24 months CA.

The study is approved by the Ethic Committee of Northern Norway (REK nord: 2009/916-7).

### Part one

#### Study sample

Prematurely born infants at the University Hospital Northern Norway HF, Tromsø, Norway, and University Hospital Trondheim HF, St. Olavs Hospital, Norway, with gestational age (GA) at birth ≤ 32 weeks are eligible for the study. The infants must be able to tolerate handling at postmenstrual age (PMA) week 34 and their parents have to understand/speak Norwegian. In addition it is required that the follow-up program takes place at the respective hospitals outpatient clinics. Exclusion criteria are triplets or higher plurality, major malformations or recent surgery.

#### Sample size calculations

Power calculation was performed. Our outcome measure at 24 months CA is the Peabody Developmental Motor Scales-2 (PDMS-2) [32]. We consider a difference on gross motor and fine motor function measured on PDMS-2 between the intervention and the control group of 0.5 SD as clinically significant. As a result there must be 63 children in each group to have an 80% chance to detect a 0.5 SD difference between the groups with a significance level of 0.05 (alpha) on two-sided tests. When we consider potential attrition and the effect of including twins, we aim to recruit 150 children, i.e., 75 in each group for part one of the study.

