##### Test instruments

Demographic data as well as information about current diseases are collected from patient records, from the NICU's online registration program and by interviewing the parents. All infants participating in the study are assessed with standardized tests at term age, three, six, 12 and 24 months CA (Figure 1). Motor development at baseline is assessed using the Test of Infant Motor Performance Screening Items (TIMPSI) at 34 weeks PMA. The TIMPSI addresses the main targets for the intervention, postural control and selective movements. The primary outcome measure is motor development at two years CA on the Peabody Developmental Motor Scales (PDMS-2). The PDMS-2 was chosen because the test assesses both fine and gross motor function, i.e., harmonizing with the intervention targets of postural control and selective movements. The PDMS-2 is also administered at six months and 12 months CA (Figure 1). Secondary outcome measures are: the General Movement Assessment (GMA) at 34 weeks, 36 weeks, and three months CA, the Test of Infant Motor Performance (TIMP) at 37 weeks, and three months CA, and the Alberta Infant Motor Scale (AIMS) at three months, six months, and 12 months CA (Figure 1).

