##### Peabody Developmental Motor Scales

The Peabody Developmental Motor Scales (PDMS-2) assesses both fine and gross motor function [32]. The test is valid from term through five years of age. PDMS-2 consists of six subtests e.g. Reflexes, Stationary, Locomotion, Object Manipulation, Grasping and Visual-Motor Integration. The results of the subtests may be used to generate three global indices of motor performance. These composites are Gross Motor Quotient, Fine Motor Quotient and Total Motor Quotient [32]. The three composites of the PDMS-2 exhibit high test-retest reliability and acceptable responsiveness to intervention effects [43]. The test is suitable to use as a motor measure for children with CP at two years of age [43].

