##### Analysis

Demographic data will be collected and described with descriptive statistics. Group differences will be analyzed using linear mixed models for continuous data and generalized estimating equations (GEE) for categorical data. These methods make it possible to account for the possible clustering effect by including twin pairs and for repeated measurements. Z-scores will be used in the longitudinal analyses as different tests are used, as the child gets older. All the tests are double sided tests and *p*-value < 0,05 is considered significant. SPSS and Stata will be used in the analyses.

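### The target difference is stated for gross and fine motor function, but the sample size is a one-comparison calculation and no single PDMS-2 score is named as primary

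*Protocol article*

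**What the plan says.** Four places in the Protocol article bear on the primary comparison.

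- **Sample size calculations** gives the clinically important difference: "We consider a difference on gross motor and fine motor function measured on PDMS-2 between the intervention and the control group of 0.5 SD". From it follows one requirement: "there must be 63 children in each group to have an 80% chance to detect a 0.5 SD difference between the groups". The test behind that figure is two-sided at the 5% level. Recruitment is then raised to 75 per group for attrition and twins.
- **Test instruments** defines the endpoint by instrument and age, not by score: "The primary outcome measure is motor development at two years CA on the Peabody Developmental Motor Scales (PDMS-2").
- **Peabody Developmental Motor Scales** lists what the instrument yields: "These composites are Gross Motor Quotient, Fine Motor Quotient and Total Motor Quotient".
- **Analysis** sets the significance level for everything: "All the tests are double sided tests and *p*-value < 0,05 is considered significant".

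None of these says whether the primary conclusion rests on gross motor, fine motor, either, both or the total score.

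**The concern.** A sample size, an alpha and a power belong to a defined test. Here the target difference refers to two functions, while the alpha and power are those of one test. With two primary variables the success rule decides which of the two figures fails. If a significant result on either function is enough, and each is tested at 0.05, the chance of a false positive conclusion exceeds 5%. If both must be significant, the chance of success when both true effects are 0.5 SD is below 80%.

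At stake is the trial's main conclusion. Without a named score, a reader of the results cannot tell which error rate and which power apply to a claim of improved motor outcome. The choice of primary variable and the sample size that goes with it are made in the protocol itself.

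**Working it through.** **Inputs.** From Sample size calculations: difference 0.5 SD, two-sided alpha 0.05, power 80%, equal groups, 63 per group. From Analysis: each test at 0.05. The correlation r between gross and fine motor scores is not given. I assume 0.3 to 0.8 and show 0 and 0.9 as outer values. Children are treated as independent, as the figure of 63 itself does.

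**Step 1: the plan's figure.** n per group = 2 × (1.960 + 0.842)² / 0.5² = 62.8, so 63. The expected test statistic is 0.5 × √(63/2) = 2.806, and the power is Φ(2.806 − 1.960) = Φ(0.846) = 80.1%. The figure is right for one comparison. (The t-test version gives 63.8, so 64, a trivial difference.)

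**Step 2: two functions, each at 0.05.** The two test statistics are taken as bivariate normal with correlation r.

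- Either suffices, no true effect: error = 1 − P(|Z₁| ≤ 1.96 and |Z₂| ≤ 1.96). At r = 0 this is 1 − 0.95² = 9.75%.
- Both required, true effect 0.5 SD on each: power = Φ₂(0.846, 0.846; r). At r = 0 this is 0.801² = 64%.

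| r (assumed) | Either suffices: type I error | Either suffices: power at 63 | Both required: power at 63 | Both required: n per group for 80% |
|---|---|---|---|---|
| 0 | 9.75% | 96% | 64% | 83 |
| 0.3 | 9.5% | 94% | 67% | 81 |
| 0.5 | 9.1% | 91% | 69% | 79 |
| 0.8 | 7.8% | 87% | 73% | 74 |
| 0.9 | 7.0% | 85% | 75% | 71 |

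The either-one rule keeps the power and loses the alpha. The both-required rule keeps the alpha and loses the power. The gap closes only as r approaches 1.

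**Step 3: splitting the alpha.** At 0.025 each, the critical value is 2.241. Power per function at 63 is Φ(2.806 − 2.241) = 71%, and 80% per function needs 2 × (2.241 + 0.842)² / 0.5² = 76.04, so 77 analysed per group. That exceeds the 75 to be recruited, and those 12 extra per group are already assigned to attrition and twins. Holm starts at the same 0.025 level. If both functions truly shift by 0.5 SD, the chance that at least one passes under Holm, 1 − P(|Z₁| ≤ 2.241 and |Z₂| ≤ 2.241), is 88% at r = 0.3 and 80% at r = 0.8. If only one shifts, its power is close to 71%.

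**Step 4: one total score.** If the stated 0.5 SD is the effect on a single score, Step 1 applies and power is 80.1%. If instead gross and fine each shift by 0.5 SD and the total behaves like their standardised sum (both assumptions), its effect is 0.5 × √(2/(1 + r)), that is 0.62 SD at r = 0.3 and 0.53 SD at r = 0.8. Power at 63 is then 94% and 84%.

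**The case against.** The best defence is that the article never declares two primary tests. Methods/Design and Test instruments both speak of one endpoint. The pair of functions appears only in the sentence on clinical importance and in the reason for choosing the instrument. Read that way, gross and fine motor function are what the Total Motor Quotient measures together, and 63 per group, 80% and 0.05 are all correct. This stands as a possible reading, and it is why the finding is conditional. It does not settle the matter, because the sample size paragraph never mentions a total score.

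A second defence is that multiplicity rules are commonly left to an analysis plan that is not shown here. That also stands: a missing adjustment is not the point. But a later rule would not repair the power statement for two primaries. An alpha split lowers power per function to about 71%, and requiring both lowers joint power to 67% to 73%.

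Third, the level in Analysis covers all tests, secondary scales included. It is a nominal level and not a rule for declaring the trial positive. A reader might infer that any of the three composites may carry the claim, but no section says so, and I give no error rate for such a rule. Nor is it supported to say flatly that the false-positive risk is nearly double. That fits only weakly correlated scores and only the either-one rule.

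**Conclusion.** The point holds in conditional form. The target difference names two functions, the calculation is for one comparison, and the primary score is left open among three composites. If gross and fine motor are both primary with each tested at 0.05, the stated alpha and power cannot both be right. The size is a type I error of 9.5% to 7.8% where either suffices, or a power of 67% to 73% where both are required, at 63 per group. These ranges rest on an assumed correlation of 0.3 to 0.8 and, for power, on a true 0.5 SD effect in each function. The two failures belong to alternative rules and do not occur together.

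A reader might conclude that the protocol fixes two primary tests. It does not: it suggests them in one sentence and names a single outcome measure elsewhere. With one primary score, the stated figures stand. This should be fixed rather than must be fixed, and confidence is medium.

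**What to change.** Before unblinding, name one primary variable at 24 months corrected age and state that the sample size refers to it. One suitable choice is the PDMS-2 Total Motor Quotient at two-sided 0.05, with the Gross and Fine Motor Quotients tested only if it is significant (in fixed order, or as a pair under Holm). This takes about one sentence and no new data, since the instrument already yields the total. The price is that a benefit confined to one domain becomes a gated secondary result.

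If the sponsor wants gross and fine motor as two primaries, state the success rule and restate the power. Under Holm that is about 71% per function at the 0.025 level with 63 analysed per group. If both are required, it is 67% to 73% jointly, with the assumed correlation given. The price is a less favourable power statement than the present 80%.

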#### Recruitment procedure

Enrollment of participants is a process taking place at the neonatal units of two Norwegian University Hospitals. Oral and written information is given to parents of the preterm babies fulfilling the inclusion criteria. Professionals not involved in the daily care and treatment of the child when the child is 33 weeks PMA conduct the interview. It is the project leader who performs the recruitment interview in Tromsø, while the representative in the project leader group in the other Hospital (St. Olavs Hospital, Trondheim) addresses the parents in Trondheim. Informed consent forms signed by the parents are delivered to a nurse or physiotherapist in the neonatal unit if the parents agree to participate, after which the baseline assessment is performed.

#### Randomization process

The infants are randomly assigned either to the intervention or to the control group. Randomization is performed by a web-based randomization system developed and administered by the Unit of Applied Clinical Research, Institute of Cancer Research and Molecular Medicine, Norwegian University of Science and Technology, Trondheim, Norway. Stratification is according to GA at birth (< 28 week and ≥ 28 weeks) and recruitment site. In the case of twins both children are randomized to the same group because of the nature of the intervention. The randomization takes place *after *the assessment of baseline motor performance (Figure 1) so that the therapists will not be biased one way or the other by knowing the group assignment.

**Figure 1 F1:**
[figure not shown]
**Flowchart of the quantitative study, part one**.

#### Intervention

##### Practitioners

Experienced physiotherapists in pediatrics are implementing the intervention and perform the assessments. In each research centre two physiotherapists are dedicated to performing the baseline assessment and teaching the treatment protocol to the parents of the intervention group infants. Each therapist maintains records (log) over the number of clinical consultations with the individual child and parent and notes what has been emphasized in the consultations. Two other physiotherapists blinded to group assignments perform the follow up assessments when the child is at term and at three, six, 12 and 24 months CA. The physiotherapists are assessed for rater reliability for the standardized tests used.

##### Content of intervention

The intervention involves education of parents in individualized handling and motor stimulation of their child. The handling and motor stimulation program is primarily based on Girolami and Campbell [6], and the performance is integrated into communication and social interaction between the caregiver and the infant [5]. The parent at the bedside of the child during the NICU admission period is the one carrying out the daily intervention after being taught by the physiotherapist. The objective of the intervention in which the main elements are postural support and movement facilitation techniques, is on improving symmetry of posture, muscle balance, and movement in infants, all of which are supporting the foundation of the execution of functional activities in the infant's daily life. The facilitating technique is intermittent adjusted pressure/compression over relevant muscle groups and joints when the infant is in supine (Table 1), prone (Table 2), sidelying (Table 1) and in supported sitting (Table 2). There are also transition activities in which the infant is guided from supine to sidelying and from supine through sidelying to upright supported sitting (Table 1). The physiotherapist chooses appropriate exercises and modifies handling for each infant's level of development and tolerance for movement; the intervention always includes one or more activities in each position. A main goal is development of head and trunk control in each position.

**Table 1 T1:** The protocol for promotion of postural and selective control of movements, supine and sidelying

Objectives	Performer activity	Activity goals for the child
1. Increase strength, balance. Control of the anterior and posterior neck muscles.	1. Activating neck flexors, shoulder and abdominal muscles through intermittent caudal compression.	1. Maintain head in midline and head turning to both sides.
2. Increase strength and control of the anterior shoulder and chest muscles and balance between anterior and posterior shoulder and chest muscles.	2. Horizontal intermittent pressure through the shoulders. Assist the child to bring arms forward to the mouth or on chest.	2. Bringing hands forward, hands to mouth and hands on chest.
3. Increase strength and control of the abdominal muscles.	3. Through lifted pelvis and flexed legs, provide intermittent compression toward shoulder.	3. Antigravity pelvis and lower extremity lifting with hip and knee flexion
4. Affect alignment, righting reactions and antigravity muscle activity in the trunk in the sagital and frontal planes.	4. From the lifted pelvis and control at shoulders, shift the infant's weight in small increments from side to side. When possible allow the infant to control the head and arms without assistance.	4. Rolling from supine to side.
5. Affect alignment, righting reactions and balance and control between the anterior and posterior neck and trunk muscles.	5. Guide the child from supine through sidelying to upright sitting.	5. Maintaining head control in midline during the transition with minimal assist.
6. Increase strength of the anterior neck muscles lateral head righting and neck and cervical extensors when rolling into prone.	6. Guiding upper shoulder slightly backwards with small weight shifting movements while supporting the child with one hand under head.	6. Keep the chin tucked during movements from supine to prone and when in sidelying
7. Increase the strength of the anterior chest and shoulder muscles.	7. Horizontal intermittent compression through the shoulders. Assist the infant in bringing the hands to mouth or toward the midline.	7. Bring hands to mouth or bring hands forward to chest.
8. Elongation of thorax and lumbar muscles; increase strength, balance and control of abdominal and trunk muscle groups.	8. Lifting pelvis laterally upward to lengthen the weight-bearing side of trunk and activate lateral muscles of the trunk and head on the non-weight-bearing side. Facilitate rolling from supine to side. Head, neck, trunk and pelvis are in alignment.	8. Maintain the pelvis in a neutral position while flexing the hip and knee. Improved antigravity strength of the lateral neck and trunk muscles

1-5: The child is in supine. 6-8: The child is sidelying

**Table 2 T2:** The protocol for promotion of postural and selective control of movements, prone and sitting

Objectives	Performer activity	Activity goals for the child
1. Increase strength, balance and control in the anterior and posterior neck and upper back muscles.	1. Intermittent compression through shoulders in caudal direction is used to activate the neck muscles, pectoralis muscles and upper back extensors.	1. Lifting the head from the surface and turning the head to right and left side.
2. Increase strength and balance of the anterior and posterior shoulder muscles.	2. Mild intermittent horizontal compression through shoulders to activate the anterior and posterior shoulder and scapular muscles.	2. Bring the hands to mouth.
3. Downward rotation and stabilization of the scapula.	3. Small weight shifts to one side to facilitate head turning by providing compression down the non-weight-bearing side and elongation of the weight-bearing side.	3. Strength and control of shoulder girdle to provide a stable base for head lifting and turning.
4. Increase activity and strength of the abdominal muscles.	4. Support and tactile input over the abdominal muscles to increase activation in the sagital and frontal planes.	4. Maintain the pelvis in neutral to provide stable base of support for trunk extension and sagital and frontal plane weight shifts.
5. Increase strength and control of neck muscles; elongation of cervical spine.	5. Intermittent compression through the shoulders in a caudal direction to facilitate balanced activation of the anterior and posterior neck, chest and abdominal muscles.	5. Maintain the head up and in midline.
6. Increase strength, balance and control of anterior and posterior neck muscles and downward rotation of the scapula.	6. Intermittent horizontal compression through shoulders and chest muscles to assist the infant to bring the hands together in midline or to the mouth.	6. Maintenance of scapular depression to assist in bringing hands to midline.
7. Integrate control of abdominal muscles and back extension muscles; increase the strength of abdominal muscles; improve balance of trunk flexor/extensor muscle activity.	7. Support the head and shoulders and tip the infant approximately 15 degrees backward to activate neck and abdominal muscles. From this position add very small lateral movements to activate trunk in the frontal plan, elongating the weight-bearing side of the body to promote lateral righting of the head and trunk.	7. Maintain capital flexion, chin toward the chest with hips and knees in neutral flexed position.

1-4: The child is in prone. 5-7: The child is in sitting

Functional goals and activities for the child in supine include: maintaining head in midline, rotating the head to right and left, bringing hands to mouth and hands to chest, adjusting their own position, turning from supine to side (Table 1). Sidelying activities include maintaining a comfortable position with head flexed toward chest, bringing hands to mouth (Table 1). Prone activities include assisting the infant to lift and turn the head to the middle and to right and left sides, adjust their position, take weight on forearms, bring the hands to the mouth, look for the caregiver (Table 2). Finally, supported sitting activities include maintaining controlled upright and midline posture of the head with good trunk extension, being able to turn the head to track and using the arms for forward reaching (Table 2).

Intervention is carried out for up to ten minutes, twice a day, over a period of three weeks (PMA weeks 34, 35, 36). During intervention the infant should be in "State of arousal level" three (eyes open, no movements) or four (eyes open, large movements) according to Prechtl's states [33]. The length of each treatment session is adjusted depending on the infant's response and condition. Intervention is terminated if the infant shows any of the following signs which are interpreted as expressions of stress or discomfort: makes faces, changes skin color, has irregular respiration, undesired changes in muscle tone, uncontrolled movements or continual changes in the state of arousal level. Performance time is adjusted to the infant's daily rhythm. Intervention may be carried out half an hour before a meal, between two meals or any time when the child has a state of arousal level of three or four. Parents record the time of each intervention and the number of interventions each day. If necessary they note concisely why intervention was not completed. At the very beginning of the intervention period parents receive a "play book" in which they find pictures and written explanations of each "exercise" they will be performing during the intervention period. The parents have to demonstrate their ability to do the activities the second and the eighth day of the intervention.

